**Fig. 3 Fig3:**
[figure not shown]
Functional Tasks. **a**. Drinking; **b**. Brushing the hair; **c**. Putting a coin inside a pot. 1. Initial phase; 2. Manipulation phase; 3. Terminal phase

The UL kinematics calculations will be computed with Upper Limb Evaluation in Motion Analysis software (https://github.com/u0078867/ulema-ul-analyzer) according to ISB recommendations. The following spatiotemporal variables will be calculated for each joint angle per phase: phase duration (second), relative phase duration (ratio between phase duration and total task duration in percentage), peak velocity (mm/s) [53, 54], time to peak velocity, and trajectory deviation (ratio between length of the travelled wrist path and the length of a straight-line connecting start and endpoint) [5, 58–61]. Furthermore, the following will also be calculated: starting angles, range of motion (the difference between the minimum and maximum angle), and joint angles at the point of task achievement (the angle required to complete the task). Hand markers [56] will be used to calculate the maximum aperture between the thumb and second finger, and the time until maximum aperture and the aperture before touching the object will also be calculated.

### Quality of life

The stroke specific of quality of life scale (SS-QOL) [62] assesses of the quality of life in individuals’ poststroke. The instrument has 49 items in 12 subscales (energy, family roles, language, mobility, mood, personality, self-care, social roles, thinking, upper extremity function, vision, and work/productivity). Five response options are offered for each item, with item scores ranging from 1 to 5. Thus, the minimum overall score on the questionnaire is 49 (lowest social participation), and the maximum score is 245 (highest social participation). The SS-QOL has good internal consistency, discriminant validity, criterion validity, concurrent validity, and test-retest reliability [63].

### Intervention protocols

The risk to participants in both intervention groups is minimal and similar to what would be encountered while participating in physical therapy or cardiac rehabilitation. The risks include the feeling of discomfort due to fatigue, the destabilization of vital signs, and frustration due to the difficulty of the tasks. More specifically, participation will be interrupted if they present pain during the procedure, postural hypotension, angina, marked changes in systolic blood pressure (systolic blood pressure ≤ 100 mmHg or > 220 mmHg and diastolic blood pressure < 60 mmHg or > 110 mmHg) or heart rate (maximum heart rate, heart rate max, = 220-age for men or 210-age for women; also, percentage of oxygen < 96% or effort perception > 5 points in the Borg scale (0–10) [64]. When the protocol results in fatigue, frustration or changes in vital signs, the test/training will be paused, and the participant will be further evaluated. If necessary, the participants will be transported to the nearest health unit.

### Aerobic exercise

Aerobic exercise (AE) will be conducted according to the American Heart Association recommendations and based on cardiopulmonary exercise testing [42, 43]. The AE will be performed on a stationary bicycle. During the AE, blood pressure, heart rate, and the perceived effort on the Borg scale–CR10 [51] will be monitored. Measures will be taken every four minutes during training. The AE will be performed at moderate to high-intensity intervals. The AE protocol will involve 10 min of warm-up in a range of 45% HRreserve, 24 min of interval training, followed by 6 min of cooldown between 45 and 60% HRreserve [65–67]. During interval training, every four minutes, the intensities will be alternated between moderate and high (75–90% HRreserve), and the recovery periods will be in moderate intensity (60% HRreserve). In both groups, individuals will receive standardized verbal feedback every 4 min, “Go on, you’re doing well!”. Individuals who do not reach the target moderate and high intensities of HRreserve during training (75–90%) will be encouraged to maintain at least moderate HRreserve intensity (60%). In addition, if the perceived effort limits target HR frequencies, then the participants will be invited to rest for some minutes and return to training until the total time of the protocol is complete. Participants will have a 10-min rest and then begin the m-CIMT protocol. Hydration will be provided to participants throughout the treatment session.

### Control therapy

To equalize participant-to-therapist interaction between groups and reduce the effect on study outcomes, participants in the Stretching + m-CIMT group will also be assisted in performing 40 min of exercise. The exercise will consist of bilateral, intermittent, passive muscle stretching, 3 repetitions with 30-s duration and 60-s intervals between each repetition will be performed for each stretching exercise on the floor or seated. The stretches will be executed for the following muscle groups: hip flexors, knee extensors, ankle flexors, elbow flexors, wrist and fingers flexors.

#### Modified Constraint-Induced Movement Therapy

Modified Constraint-Induced Movement Therapy (m-CIMT) will begin 10 min after the patients have completed the AE or stretching session. The protocol consists of intensive training for 3 h per day for 10 days (two weeks, excluding weekends) and has three components: (1) intensive graded task-oriented training of the paretic upper limb; (2) restriction of the unaffected upper extremity for 90% of the total number of hours awake using a glove; and (3) transfer package, which consists of a behavioral adherence method designed to transfer the gains obtained in the clinical setting to the participants’ real-world environment [15].

Intensive graded task-oriented training of the paretic upper limb includes task training with high repetitions and an increasing level of difficulty between sessions, which vary between patients (shaping). It also involves task training as a whole with a clearly defined context (task practice). The transfer package consists of a list with ten tasks that should be performed at home between each session while wearing the glove and recorded in a home diary. Moreover, in this home diary, individuals must report if they performed the activities at home using the glove and what difficulties they experienced using it. The therapist and the patient choose the tasks in this list at the beginning of the session based on their daily routine. Restraint of the less-affected upper limb will be performed with a removable glove, which allows the limb to be used for support, if necessary, but prevents grasping [40].

In each 3-h session, the use of the glove will be monitored, the MAL will be completed (the first 22 tasks on even days and the last 23 on odd days), and the transfer package will be discussed in the first 30 min. In the remaining hours, upper limb-oriented training of six tasks (six different activities for odd and even days) (Table 2) and one task-practice will be performed. The shaping tasks will vary depending on individual needs and their results in the MAL, which will be individually adjusted (more difficult compared to the previous session) by the therapist. Between each task, a 30-s rest will be given. Whole task practice will be performed to promote the increased motor function of the affected limb during functional activities.

**Table 2 Tab2:** Table of the tasks performed in shaping

Task	Materials used	Description	Emphasized Movements
Odd days			
1. 1. Put blocks on top of the box	A box and various blocks	The subject moves blocks of wood of the table into the box. The placement and height of the box depend on the desired movement.	Pinch, wrist extension, elbow extension, shoulder flexion
2. Clean the table	A flannel, ruler, scotch tape	The subject is asked to use the flannel, while doing movements of cleaning the table, at a given target.	Elbow extension, shoulder flexion, abduction or adduction depending on the placement of the target.
2. 3. Velcro parts	A checkerboard and the lady’s pieces with Velcro	The checkerboard is used with Velcro in separated houses. The lady’s pieces are of wood with Velcro below the top. The subject is asked to grasp clamp or finger extending and moving the piece from one house to another in the frame.	Pinch or isolated finger movements, wrist flexion/extension, elbow extension, shoulder flexion.
3. 4. Poker chips	A modeling clay and poker chips	The subject is asked the grasp the poker chips, one at a time and put them in the glass. The poker chips can be arranged on the darts board or on a clay mound.	Pinch, wrist extension, elbow extension and shoulder flexion.
4. 5. Open and close the door		The subject is asked to stay front of the door. The distance from the door is measured and marked. The subject practices opening and closing the closet door.	Grip, supination, extension and flexion elbow, flexion and extension shoulder.
5. 6. Placing balls	Tennis, golf ping pong balls and cup	Balls are placing in table and the subject is asked to grasp one at the time and placing in cup.	Various types of grip, elbow extension, shoulder flexion, horizontal adduction/abduction of shoulder.
6. 7. Hockey puck	A hockey puck and scotch tape	Draw a line or put a scotch tape on the table. The subject holds the *hockey puck* and pushes it to the line or to the line drawn trough the elbow extension.	Pinch, elbow extension, abduction shoulder, scapular abduction and protraction.
Even days			
7. 1. Pegboard	A pegboard	The subject raises the wooden stick and places it on a pegboard hole designed. The pegboard can be placed on top of a box to work the shoulder flexion.	Pinch, wrist extension, elbow extension, shoulder flexion.
8. 2. Pasta Roll	A pasta roll	A mark is made on the backing surface of the pasta roll and this is positioned on the table. The participant is asked to handle the pasta roll.	Pinch, ulnar and radial deviation.
9. 3. Turn dominoes	A domino	The dominoes are positioned in front of the subject. The participant is requiring to reach the pieces and turn them.	Pinch or isolated finger movements, wrist extension, supination and pronation of the forearm, shoulder flexion.
10. 4. Fork and meat	Fork, dish and modeling clay	The subject is asked when used the fork to grasp pieces modeling clay and moved to dish, one at a time. The therapist can watch by pulling the pieces of clay from the fork if necessary, but the subject should be encouraged to pull the fork while the therapist holds the clay.	Pinch, elbow extension, shoulder flexion, addition / abduction.
11. 5. Hoop horizontal	Bar and rings	The subject is required to place the rings in a horizontal position on the bar.	Pinch, wrist extension, elbow extension, shoulder flexion, horizontal abduction and adduction.
12. 6. Serve on a mug	A mug with handle, beans or marble, and a cup or bowl.	Beans or marble are placed in a mug. The subject is required to grasp the mug by the handle and pour the beans into the cup or bowl without knocking down any beans, and then put the mug back on the table.	Types of grip, wrist extension, forearm supination/pronation, elbow extension and should flexion.
13. 7. Bottle of water	Bottle of water	The subject is asked to use a cylindrical grip and moving the bottle from one target to another while keeping the forearm in a neutral position.	Cylindrical grip, supination, extension and flexion elbow, flexion and extension shoulder.

### Attrition and adherence

Participants will be withdrawn from the study under the following conditions: a) two consecutive or three alternating absences during treatment sessions; b) inability to complete the posttest and follow-up; or c) development of any disabling condition that precludes participation in the study. Regarding adherence strategies, up to two nonconsecutive absences can be compensated the following week. There will also be flexible hours offered for receiving therapy, as well as direct contact by telephone with participants confirming the evaluation dates and supporting treatment adherence. Additional measures to avoid individuals dropping out are periodic evaluations (during the outcome analyses) on the satisfaction level of the therapy, discussing difficulties in continuing treatment (for example, transport logistics to the laboratory), and attempts to resolve and prevent possible problems that may interfere with adherence and continued participation in the study. Semistructured interviews will be held with each participant.

After the initial five days of participation and following completion of the ten days of therapy. A series of open-ended questions will be asked regarding their impressions, satisfaction, and physical tolerance of the treatment.

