## Methods

This study is a randomized, single-blinded, intention-to-treat controlled clinical trial in which 78 participants of both genders in a chronic stage poststroke will be randomized into two groups of 39 participants. One group will receive AE combined with m-CIMT, and the other group will perform stretching exercises combined with m-CIMT. The eligibility criteria are presented in Table 1.

**Table 1 Tab1:** Eligibility criteria

Inclusion criteria	
• Stroke resulting in hemiparesis at least six months prior (chronic) • Do not a present lesion in the two hemispheres • Clinical diagnosis of ischemic or hemorrhagic stroke • ≥ 35 and ≤ 80 years old • Participants must present a minimum active movement of 45° of shoulder flexion or abduction, 20° of elbow extension, 10° of wrist extension, 10° of abduction or extension of the thumb, and 10° extension in at least two fingers (metacarpophalangeal and interphalangeal joints) and thumb • Participants must present the ability to pick up a towel using any grip [28] • Participants must present asymmetric of upper extremity, ≤ 2.5 in the Motor Activity Log (MAL) Quantity Scale [10] • Participants must have the ability to remain seated without trunk and arm support for 1 min [29]	
Exclusion criteria	
• Upper limb movement deficits attributable to no stroke pathology	
• Clear signs of dementia or cognitive disorder, indicated in the Mini- Mental State Examination (scores based in years of education, below 13 for illiterate individuals, 18 for individuals with 1 to 7 years of the primary school and 26 for individuals over eight years after primary school) [30, 31] • Individuals with lesion in cerebellar	
• The individuals are smokers, alcohol, or users of illicit drugs at the time of evaluation • Individuals with structural alterations in the cardiovascular and respiratory systems that will contraindicate the aerobic exercise • Individuals with uncorrected auditory and visual deficits • Individuals who present any electrocardiogram alteration or not the cardiorespiratory stress test • Individuals with historical diseases or osteomioarticular alterations • Individuals with body mass index > 28 • Individuals with uncontrolled diabetes mellitus or hypertension, comprehension aphasia, apraxia	

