### Statistical analysis

Demographic characteristics, such as weight, height and body mass index, will be presented as the mean and standard deviation. Median, maximum and minimum values will be used to describe poststroke time and UE-FMA score.

For all dependent variables, normality (Kolmogorov-Smirnov) and homogeneity (Levene) tests will be applied. If the variables present a normal and homogeneous distribution, then two-way analysis of variance with repeated measurements and Bonferroni’s correction will be used to examine the effect of group-by-evaluation time interaction, group (AE + m-CIMT and Stretching + m-CIMT), and evaluation time (baseline, 3, 30 and 90 days after the intervention). To protect against Type I error, Bonferroni’s correction will be used. Thus, each of the 10 planned comparisons will have to achieve *p* = 0.005 for statistical significance. The partial eta squared (η^2^) will be used to determine the effect size of the intervention. The mean difference from pre- and post-interventions and the corresponding 95% confidence interval (95% CI) will be calculated for each group (EA + m-CIMT and Stretching + m-CIMT) in order to estimate the effect of the intervention.

Otherwise, the Friedman test (*p* < 0.05) will be used followed by the Wilcoxon test with Bonferroni’s adjustment (*p* < 0.008) to compare evaluation time for each group baseline, 3 days, 30 days, 90 days after the end of treatment. The Mann-Whitney test with Bonferroni’s adjustment (*p* < 0.012) will be used to compare the groups in each time evaluation (EA + m-CIMT and Stretching + m-CIMT).

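### The trial is labelled intention-to-treat, but its withdrawal rules take randomised participants out of the study, and the four-visit tests then leave what is in effect a completers analysis

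*Protocol article*

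**What the plan says.** The Methods section of the protocol article calls the trial a "randomized, single-blinded, intention-to-treat controlled clinical trial" with 78 participants, 39 per group.

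The Attrition and adherence section then lists three grounds for withdrawal:
- Rule (a): "Participants will be withdrawn from the study under the following conditions: a) two consecutive or three alternating absences during treatment sessions".
- Rule (b): "inability to complete the posttest and follow-up".
- Rule (c): "development of any disabling condition that precludes participation in the study".

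The same section softens rule (a), because "up to two nonconsecutive absences can be compensated the following week".

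For normal, homogeneous data the Statistical analysis section says "then two-way analysis of variance with repeated measurements and" Bonferroni's correction, covering baseline and 3, 30 and 90 days after the intervention. Otherwise it plans a Friedman test and Wilcoxon tests within each group, and Mann-Whitney tests between groups at each time point.

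The Sample size section allows for 20% drop-out.

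**The concern.** Intention-to-treat means that everyone randomised is followed and analysed in the allocated group, whether or not they adhere. Rule (a) ends study participation because of non-adherence after randomisation. Rule (b) makes having outcome data a condition of staying in. Taken with tests that need all four visits, these rules leave the parametric comparison resting on people who attended enough sessions and every assessment.

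That group is no longer protected by randomisation. One arm cycles at moderate to high intensity and the other is passively stretched, so the number of absences and the reasons for them could differ between arms. If they do, and if those who leave would have scored differently, the group difference is biased. On the ANOVA route, a single missed 90-day visit also discards that person's 3- and 30-day results.

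**Working it through.** **1. The sections side by side.**

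| Question | Methods | Attrition and adherence | Statistical analysis |
|---|---|---|---|
| Who counts? | All randomised, by the intention-to-treat label | Those not withdrawn under (a) to (c) | In standard form, ANOVA and Friedman keep those with all four visits |
| Does follow-up continue after stopping treatment? | Implied by the label | Withdrawal is from the study; no later assessment is provided for | Not addressed |

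The rules differ in weight. Rule (a) is the serious one, since a person who missed sessions can usually still be assessed. Rules (b) and (c) largely describe loss that no plan could avoid. The between-group Mann-Whitney tests can use everyone seen at each visit, but they too lack data for anyone whose assessments ended at withdrawal.

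**2. The plan's own figure.** The stated 78 fits a completer target plus 20% drop-out:
- per group, 31 / (1 − 0.20) = 38.75, rounded up to 39;
- in total, 62 / (1 − 0.20) = 77.5, rounded up to 78.

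The expected loss is 0.20 × 78 = 15.6, about 16 people. The article gives no effect size. Back-solving 31 per group at 85% power and alpha 0.05 gives d = 0.77 two-sided or 0.69 one-sided. This is an inference and not a planning value.

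**3. How large could the bias be?** Assumptions, none of them in the article: no true effect; outcome with SD 1; a fraction p is lost, being those lowest on a normal variable that has correlation r with the outcome. The completers' mean then shifts upward by

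shift = r × φ(z_p) / (1 − p)

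- p = 0.20: φ = 0.280, and 0.280 / 0.80 = 0.350. The shift is 0.105 SD for r = 0.3 and 0.175 SD for r = 0.5.
- p = 0.10: φ = 0.1755, and 0.1755 / 0.90 = 0.195. The shift is 0.0585 SD for r = 0.3 and 0.0975 SD for r = 0.5.

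The bias is the aerobic shift minus the stretching shift. The rejection rates come from simulated null trials with 39 randomised per arm and a two-sided t-test at 5%; they vary slightly between runs.

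| Assumed loss, aerobic / stretching | Bias, r = 0.3 | Bias, r = 0.5 | Type I error, r = 0.3 | Type I error, r = 0.5 |
|---|---|---|---|---|
| 20% / 10%, outcome-related in aerobic arm only | 0.105 − 0 = 0.105 SD | 0.175 − 0 = 0.175 SD | about 7% | about 11–12% |
| 20% / 10%, outcome-related in both arms | 0.105 − 0.0585 = 0.05 SD | 0.175 − 0.0975 = 0.08 SD | about 5.5% | about 7% |
| 20% / 20%, same mechanism | 0 | 0 | – | – |

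Against the back-solved d of 0.77, the top of the range is 0.18 / 0.77 = 23%.

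**The case against.** The strongest reply is that the article defines no analysis set and does not say that withdrawn participants are left out. Analysis sets and missing-data handling are commonly left to a fuller document, which is not shown and could specify imputation. All of that stands. A reader might infer that the plan expressly orders a completers analysis, or bars assessment after withdrawal, but no sentence says either. The conclusion follows from the withdrawal wording combined with tests that need every visit. What the reply does not remove is the conflict in wording between two sections. Nor can an analysis plan recover outcomes that the protocol has stopped collecting.

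Three further points stand. A single missed session does not lead to withdrawal: it takes "two consecutive or three alternating absences during treatment sessions", and some absences can be made up. Rules (b) and (c) mostly record unavoidable loss. The per-visit Mann-Whitney tests need not discard earlier visits.

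A reader might also infer that the bias is known to favour aerobic exercise. The article does not support this. Both arms share the heaviest burden, 3 hours of m-CIMT a day for 10 days. Aerobic participants may work at the lower intensity or rest, and candidates must take an exercise test. Outcome-related loss in one arm only is an assumption. The 20% / 10% scenario averages 15% loss, below the plan's 20% allowance, and its error rates are at 5%, not at the adjusted thresholds (0.005, 0.012) in the Statistical analysis section.

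**Conclusion.** The concern holds in this form: the study-withdrawal wording, chiefly rule (a), conflicts with the intention-to-treat label, and with ANOVA or Friedman in standard form the main analysis is in effect one of completers.

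The resulting bias cannot be sized from the document. Under the stated assumptions it runs from zero (equal loss, same mechanism), through 0.05–0.08 SD (20% against 10%, outcome-related in both arms), to 0.10–0.18 SD (outcome-related in the aerobic arm only). Across the unequal-loss scenarios type I error is about 5.5% to 12% at a nominal 5%. Its direction is also unknown; the positive sign in these scenarios comes from assuming that poor performers are the ones who leave. The point should be fixed before outcomes are lost, but the document does not show that the result will be biased.

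**What to change.** 1. Reconcile the Methods and the Attrition and adherence sections by separating stopping study treatment from leaving the study. The criteria for stopping treatment need not change.
2. State that every randomised participant will still be invited to the 3-, 30- and 90-day assessments unless consent is withdrawn.
3. Analyse everyone in the allocated group with a method that keeps partial data, for example a likelihood-based linear mixed model with visit as a factor. Report the completers analysis as a sensitivity analysis.

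The second step is the essential one. A mixed model retains the visits that were made, but by itself it does not correct loss that depends on unobserved outcomes, which is the mechanism in the scenarios above.

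The cost is a change of wording plus some effort to bring back people who stopped treatment. Each assessment spans two days, so an upper bound, if all 16 expected losses occurred during treatment and all returned three times, is 16 × 3 × 2 = 96 assessment days. These assessments are already planned for all 78 participants, and no one extra needs to be recruited.
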